### Trial design {8}

INFERR is a multi-centre, parallel group, prospective open-label blinded endpoint randomised controlled superiority trial which compares intervention intravenous iron therapy and control group receiving standard care in adult First Nations Australians on MHD with a serum ferritin of over 700 μg/L (Figs. 1 and 2).

**Fig. 1 Fig1:**
[figure not shown]
Overview of INFERR trial design

**Fig. 2 Fig2:**
[figure not shown]
INFERR Clinical trial design and treatment allocation

## Methods: participants, interventions and outcomes

### Study setting {9}

The study is conducted in all the nine renal haemodialysis units across the Northern Territory (NT) of Australia where over 85% of dialysis patients are First Nations Australians. First Nations Australians on MHD for over 3 months are recruited in the study. Participating units include the 7A Dialysis Unit at the Royal Darwin Hospital, Nightcliff and Palmerston renal dialysis units in Darwin, Katherine Dialysis unit, Tiwi Islands Dialysis unit, Tennant Creek Dialysis unit, the inpatient renal ward at Alice Springs Hospital and the Gap Road and Flynn Drive Dialysis units in Alice Springs.

### Eligibility criteria {10}

Participant inclusion criteria include the following: [1] male or female aged ≥ 18 years old [2]; identify as Aboriginal and/or Torres Strait Islander (First Nations) [3]; on maintenance haemodialysis for ≥ 3 months [4]; the following clinical laboratory results: (a) haemoglobin ≤ 115 g/L, (b) ferritin levels between ≥ 700 μg/L and ≤ 2000 μg/L, (c) TSAT < 40%, (d) CRP < 50 mg/L [5]; willing to join the study and can provide informed consent; and [6] on adequate erythropoietin-stimulating agent (ESA) therapy.

The following are the participant exclusion criteria: [1] History of known allergic or adverse or hypersensitivity reactions to iron polymaltose [2]; already receiving iron unless stopped for ≥ 4 weeks at the time of recruitment [3]; have received blood transfusion within the last 4 weeks [4]; known iron overload, haemochromatosis, haemoglobinopathy, haemolytic anaemia, aplastic anaemia, lymphoproliferative disease or cancer or on current cancer treatment [5]; participant’s primary clinician unwilling to enrol [6]; not planning to remain resident in the NT for at least 12 months [7]; ferritin > 2000 μg/L [8]; TSAT ≥ 40% [9]; CRP ≥ 50 mg/L [10]; life expectancy < 6 months based on the judgement of the investigator [11]; living-donor transplant scheduled within 12 months; and [12] Scheduled to switch to peritoneal dialysis.

Temporary exclusion criteria are as follows: The participant may not enter the trial at any given time if fever > 38 °C, or has evidence of active bacterial infection, or CRP ≥ 50 mg/L and current severe acute asthma, eczema and any allergies. These can be considered once these have normalised and are under control.

### Who will take informed consent {26a}

The consent process is carried out by the study team of trained research nurses delegated the responsibility by the principal investigator with the assistance of an Aboriginal research assistant. The research team explains the rationale and methodology of the study face to face to potential study participants from the dialysis patients and their families and carers. Patients and their families and carers are given the opportunity to ask questions and consider whether to participate in the trial. An informed consent discussion is held with each participant. The information for the discussion is provided in written and oral formats that have been approved by the Human Research Committees (HRECs) and in a language comprehensible to the potential participant, using interpreters where indicated.

The information presented details the exact nature of the trial and what is expected of the participant including any risks or benefits in taking part. It is clearly stated that the participant is free to withdraw from the trial at any time for any reason without prejudice to future care, and with no obligation to give the reason for withdrawal. The participants are allowed ample time to go through the Participant Information Sheet and ask questions.

The participant personally signs and dates the latest approved version of the consent form, as will the investigator or the delegated study team member (who conducted the consent discussion). If one was used, an interpreter also signs and dates the consent form. Where the participant is illiterate, they can sign the consent form with their mark rather than their signature. A witness must be present during the entire consenting process and must be able and willing to sign the consent form also. A copy of the Participant Information Sheet and consent form is provided to the participant. No trial-related procedure is undertaken before documented informed consent is obtained. The original copy of the consent form is retained in the Investigator Site File (ISF) at the recruitment site and a copy placed in the patient’s medical records. The person conducting the consent discussion will document this in the participant’s medical record and enter data into the Day 1 Case Report Form (CRF)

### Additional consent provisions for collection and use of participant data and biological specimens {26b}

Additional consent will be obtained for the FerriScans for the determination of liver iron, ultrasound scans of the liver and liver FibroScans for the determination of any liver disease.

## Interventions

### Explanation of choice of comparators {6b}

In the standard clinical protocol used by dialysis units across the NT for patients with ferritin < 700 μg/L and TSAT < 40%, a maximum dose of 400 mg of IV iron once monthly is used and is based on the best current evidence for iron administration in haemodialysis patients based on the results of the PIVOTAL trial for dosing IV iron in haemodialysis patients [46] (see additional file 1). Using this protocol, participants in the study will receive either IV iron 400 mg every month (200 mg during 2 consecutive haemodialysis sessions) or no IV iron as the comparator.

### Intervention description {11a}

#### Treatment of study participants

Participants are randomised to either Arm A: Intervention IV Iron treatment group (Figs. 1 and 2), or Arm B: Control group receiving no intravenous iron treatment (Figs. 1 and 2). After the randomisation, participants receive monthly treatment as per their randomisation of either monthly intravenous iron if serum ferritin ≥ 700 μg/L and ≤ 2000 μg/L and TSAT < 40% (Arm A) or no IV iron treatment (Arm B) for up to 36 months. Study treatment is withheld if monthly testing demonstrated ferritin > 2000 μg/L and/or TSAT ≥ 40%. These markers will be measured prior to administration of Arm A or B treatment. For both Arms A and B, if the serum ferritin level is < 700 μg/L and TSAT < 40%, rescue therapy is administered. All treatment is administered during dialysis via the ports on the dialysis circuits (see additional file 2).

#### Intervention treatment Arm A and the control Arm B

Intravenous iron polymaltose is administered according to the standard clinical protocol during haemodialysis. For Arm A, patients receive IV iron polymaltose 200 mg during each of the first 2 haemodialysis sessions at the start of the study, and during each of the first 2 dialysis sessions of the week following the monthly blood tests for all subsequent months (i.e. 400 mg per month). If monthly testing demonstrates ferritin > 2000 μg/L and/or TSAT ≥ 40%, IV iron is withheld for the month. The IV iron is restarted as per protocol when the monthly tests demonstrate ferritin > 700 μg/L and ≤ 2000 μg/L and TSAT < 40%. Rescue therapy of 400 mg of iron polymaltose is administered intravenously on haemodialysis if ferritin ≤ 700 μg/L and TSAT < 40% or as indicated by the treating nephrologist (see below). If monthly testing demonstrates ferritin > 700 μg/L and ≤ 2000 and TSAT < 40%, patients will continue with their allocated randomised treatment (Fig. 2).

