**Methods:**

In a prospective open-label blinded endpoint randomised controlled trial, a total of 576 participants on maintenance haemodialysis with high ferritin (> 700 μg/L and ≤ 2000 μg/L) and low transferrin saturation (< 40%) from all the 7 renal units across the Northern Territory of Australia will be randomised 1:1 to receive intravenous iron polymaltose 400 mg once monthly (200 mg during 2 consecutive haemodialysis sessions) (Arm A) or no IV iron treatment (standard treatment) (Arm B). Rescue therapy will be administered when the ferritin levels fall below 700 μg/L or when clinically indicated. The primary outcome will be the differences between the two study arms in the risk of hospitalisation with all-cause infection or death. An economic analysis and several secondary and tertiary outcomes analyses will also be performed.

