### Criteria for discontinuing or modifying allocated interventions {11b}

#### Rescue therapy

For both Arms A and B, if monthly blood tests demonstrate ferritin **<** 700 μg/L and TSAT **<** 40%, 200 mg of intravenous iron polymaltose is administered during each of the first two haemodialysis sessions in the second week after the monthly blood tests. When the monthly blood tests indicate ferritin **>** 700 μg/L and ≤ 2000 μg/L and TSAT **<** 40%, the rescue therapy will be ceased, and participants continue to receive their allocated study treatment.

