#### Safety

All the trial medications are licenced for use in Australia with established safety profiles and routinely used in clinical practice. A safety measure was written into the protocol to avoid putting participants at risk of either excessive or insufficient IV iron administration according to the current standards for haemodialysis patients. Prior to receiving any study treatment, participants’ blood results are reviewed for ferritin and TSAT levels; participants’ treatment varies based on the results of these blood levels:
Assigned study drug will be administered for ferritin levels between ≥ 700 μg/L and ≤ 2000 μg/L and TSAT < 40% and ferritin < 700 μg/L and TSAT < 40% (Arm A) and no treatment for ferritin levels between ≥ 700 μg/L and ≤ 2000 μg/L and TSAT < 40% (Arm B) and rescue therapy for ferritin levels < 700 μg/L and TSAT< 40% (both arms)For both Arms A and B, if ferritin levels are < 700 μg/L *and* TSAT < 40%, “rescue treatment” will be administered for that month.If ferritin > 2000 μg/L and/or TSAT ≥ 40% for both Arms A and B, study treatment will be withheld and receive no treatment for that month.

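### Rescue iron has a laboratory-only trigger in three sections and an added, unbounded clinician trigger in two others, and the protocol does not say which governs at ferritin 700 to 2000 μg/L or when treatment is withheld

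*Protocol article*

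**What the plan says.** **Laboratory-only trigger, both arms**

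- *Treatment of study participants*: "For both Arms A and B, if the serum ferritin level is < 700 μg/L and TSAT < 40%, rescue therapy is administered".
- *Rescue therapy*: under the same ferritin and TSAT condition on the monthly tests, "200 mg of intravenous iron polymaltose is administered during each of the first two haemodialysis sessions in the second week" after those tests. No other trigger is given.
- *Safety*: "rescue therapy for ferritin levels < 700 μg/L and TSAT< 40% (both arms").

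**Laboratory trigger plus clinician trigger**

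- *Intervention treatment Arm A and the control Arm B*: "Rescue therapy of 400 mg of iron polymaltose is administered intravenously on haemodialysis" on the laboratory condition, "or as indicated by the treating nephrologist (see below").
- Abstract, *Methods*: "Rescue therapy will be administered when the ferritin levels fall below 700 μg/L or when clinically indicated".

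**Text that limits rescue**

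- In the arms section, the sentence straight after the clinician clause keeps patients on their randomised treatment when ferritin is above 700 and up to 2000 μg/L with TSAT below 40%. *Rescue therapy* says that rescue stops in that range.
- When ferritin exceeds 2000 μg/L and/or TSAT is 40% or more, *Treatment of study participants* and *Withholding of therapy* withhold study treatment. The arms section withholds IV iron for the month. *Safety* says "study treatment will be withheld and receive no treatment for that month".

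**Context**

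Arm A receives 400 mg a month as two 200 mg doses, and Arm B receives no IV iron (*Explanation of choice of comparators*). Patients, nurses and investigators know the allocation (*Who is blinded*). The primary analysis is by intention to treat. The per-protocol set consists of those who completed their allocated treatment.

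**The concern.** Whether a clinician may trigger rescue iron, and at what ferritin and TSAT, has two answers in this protocol. Rescue iron and Arm A's treatment are the same product at the same monthly dose, so the answer decides how far apart the two arms are kept.

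Take an Arm B patient with falling haemoglobin, ferritin 1100 μg/L and TSAT 18%. Under the three laboratory-only sections this patient gets no iron. Under the clinician clause read alone, an unblinded nephrologist may give what Arm A gets and record it as rescue. Two sites could follow different sentences, and each could claim to be following the protocol.

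Two analyses are exposed. Intention to treat keeps such a patient in Arm B, which pulls the hazard ratio and the haemoglobin difference towards no effect and would attenuate either a benefit or an infection harm. The per-protocol set cannot be applied consistently while it is unclear whether clinician-triggered iron counts as allocated treatment. The monitor, who must verify that patients received study drug as randomised, faces the same ambiguity.

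**Working it through.** **1. The text, case by case, for an Arm B patient**

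| Monthly result | Laboratory-only sections | Clinician clause read alone | Other text |
|---|---|---|---|
| Ferritin < 700, TSAT < 40% | Rescue | Rescue | Agrees |
| Ferritin > 700 to 2000, TSAT < 40% | No rescue | Rescue possible | Allocated treatment continues; rescue stops |
| Ferritin > 2000 and/or TSAT ≥ 40% | No rescue | No limit stated | Study treatment withheld (two sections); IV iron withheld (arms section); no treatment (*Safety*) |

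The first row is consistent, apart from the arms section including a ferritin of exactly 700 μg/L where the laboratory-only sections use below 700. The second row is a direct conflict, part of it between adjacent sentences of one section. In the third row no sentence states how clinician-triggered rescue relates to withholding. The cross-reference attached to the clinician clause would resolve this if its target gave a criterion, but *Rescue therapy* gives none.

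**2. The protocol's own power figure**

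Inputs from *Sample size*: 60% against 48% at 2 years, 5% significance (taken as two-sided), more than 80% power, 5% drop-out, 576 participants (a total, as the abstract states).

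- Two proportions at 80% power: 270 per arm, 540 in total; 540/0.95 = 569, close to 576.
- Evaluable: 576 × 0.95 = 547, or 273.6 per arm.
- Power for two proportions with 547: 80.6%.
- Log-rank (Schoenfeld): HR = ln 0.52/ln 0.40 = 0.714. Events D = 547 × (0.60 + 0.48)/2 ≈ 295. Power = Φ(|ln HR|·√D/2 − 1.96) = 82.6%.

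The stated power of more than 80% is reproduced.

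**3. Illustration of dilution**

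The documents give no rate of clinician-triggered rescue, so the fraction below is an assumption, as is a full iron effect in those who receive it.

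- Patient model: a fraction c of Arm B has the Arm A risk from randomisation, so the control rate is 0.60 − 0.12c. At c = 0.10 it is 0.588, HR = ln 0.52/ln 0.412 = 0.737 and D = 547 × (0.588 + 0.48)/2 ≈ 292.
- Time model: a fraction f of Arm B time is on iron, so HR = 0.714/[(1 − f) + 0.714f]. At f = 0.10, HR = 0.735. Events are held at 295, a simplification that slightly favours power.

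| Assumed fraction | Patient model, two proportions | Patient model, log-rank | Time model, log-rank |
|---|---|---|---|
| 0 | 80.6% | 82.6% | 82.6% |
| 10% | 71.8% | 74.0% | 75.5% |
| 20% | 61.4% | 63.6% | 66.7% |

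At an assumed 5% the patient model already gives 76.4% (two proportions) or 78.6% (log-rank). The sample size allows for 5% drop-out and states no allowance for crossover.

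**The case against.** The strongest reply is that the protocol contains the limits the concern says are missing. The sentence after the clinician clause keeps patients at ferritin 700 to 2000 μg/L on allocated treatment, *Rescue therapy* says rescue stops there, and both the arms section and *Safety* read as flat bars on iron during withholding. This stands against two stronger conclusions that a reader might draw. One is that iron given to Arm B in that range is expressly protocol-compliant. The other is that the withholding safeguard can be bypassed. The documents permit neither outright; they leave a conflict unresolved.

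A second reply is that the abstract condenses, and that Fig. 2 and the additional files are not shown, so a clinician criterion may exist elsewhere. That is possible, and an unbounded rule is not proven. But the conflict lies within the operative sections themselves, and the article says that it provides the full study protocol.

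Third, a reader might infer that discretionary iron will be commoner in Arm B. Iron is hypothesised to raise haemoglobin, so this is plausible. But both arms enter with haemoglobin at or below 115 g/L, ESA dosing can be adjusted, and no data are given. Nor would partial crossover hide a harm entirely; it would attenuate it.

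Fourth, much of the monitoring exists: cumulative iron dose by arm every 3 months, regular record checks, compliance data in the CRFs, site monitoring, DSMB oversight and a per-protocol analysis. This stands, and a supplementary analysis may properly sit in an analysis plan that is not shown. But cumulative dose alone does not show why iron was given, and none of these provisions says which rescue rule applies.

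**Conclusion.** The inconsistency is real and should be corrected. Three sections give a laboratory-only trigger, while the arms section and the abstract add a clinician trigger without bounds, with a cross-reference that leads to no criterion. It matters because rescue and intervention are the same 400 mg, the control is no IV iron, and treating staff are unblinded.

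The conclusion is limited to an unresolved conflict about ferritin 700 to 2000 μg/L and an unstated relation to withholding. It does not rest on the power figures. Those show only what would follow under an assumed crossover of 10 to 20% with full iron effect: power of roughly 61–76%, against 81–83% without crossover. They are not evidence that crossover will occur or at what rate.

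**What to change.** - Reconcile the abstract, *Treatment of study participants*, *Intervention treatment Arm A and the control Arm B*, *Rescue therapy*, *Withholding of therapy* and *Safety*, so that one set of rescue triggers, and its relation to withholding, holds in every section and both arms. Which rule applies is for the investigators to decide.
- Give the cross-reference a target, or remove it, in line with that decision.
- For each non-allocated iron dose in either arm, record the trigger (laboratory rule or clinician decision) and the ferritin and TSAT at the time, and report these by arm.
- State how such doses count for the per-protocol set under the reconciled rule.
- Add a supplementary analysis that accounts for clinician-triggered iron in Arm B, keeping intention to treat as primary. The analysis plan is a suitable place for it.

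The cost is a wording amendment, one extra CRF field for the trigger and one further analysis. Reported adherence may look less favourable once these doses are identified.

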### Criteria for discontinuing or modifying allocated interventions {11b}

#### Rescue therapy

For both Arms A and B, if monthly blood tests demonstrate ferritin **<** 700 μg/L and TSAT **<** 40%, 200 mg of intravenous iron polymaltose is administered during each of the first two haemodialysis sessions in the second week after the monthly blood tests. When the monthly blood tests indicate ferritin **>** 700 μg/L and ≤ 2000 μg/L and TSAT **<** 40%, the rescue therapy will be ceased, and participants continue to receive their allocated study treatment.

#### Withholding of therapy

For both arms, if monthly blood tests demonstrate ferritin ***>*** 2000 μg/L and/or TSAT ≥ 40%, study treatment is withheld. When the monthly blood tests indicate ferritin ≤ 2000 μg per litre and TSAT ***<*** 40%, patients continue to receive their allocated study treatment.

### Strategies to improve adherence to interventions {11c}:

#### Training of site nurses and nephrologists

All site staff at each participating dialysis unit are trained in the study protocol, Standard Operating Procedures (SOPs) and their reporting requirements by the Clinical Trial Manager or trained research nurse, a study chief investigator or delegate, prior to the site being opened for recruitment. All site investigators complete a computer-based training course in Good Clinical Practice and assist in providing robust training to their respective site staff.

The Clinical Trial Manager or delegate have regular phone, email or video conferencing contact with each participating dialysis unit.

### Relevant concomitant care that are permitted or prohibited during the trial {11d}

#### ESA therapy

All patients should be on adequate ESA dose at the time of randomisation. The ESA dose is determined according to the routine ESA dosing protocol. ESA dosing can be adjusted by the caring clinical teams as per the usual ESA administration protocol***.***

#### Documentation in patient’s medical record

A sticker is placed in the patient’s dialysis medical record (one on the progress notes on the day of randomisation, and one in the front inside cover of the dialysis record and on the medical record [“old notes”] if one exists). This sticker will alert clinicians that the patient has been randomised to the INFERR study, with a brief explanation of the study, and confirmation that the participant has provided written informed consent.

A copy of the study synopsis is also placed in the medical notes of the patient. A checklist of study procedures is also placed in the notes.

For electronic medical records, an electronic “sticker” is used, and appropriate annotations are made in the Primary Care Information System (PCIS) as well as letters in the Clinical Workstation (CWS). This is routine practice for all patients within the NT renal services.

#### Checking of medical records

The medical records (paper or electronic) are checked 3 months post randomisation (± 1 month) and at least 3 monthly (± 2 months) thereafter for up to 36 months by the study team to ensure adherence to the study protocol.

### Provision for post-trial care {30}

Participants found to have evidence of liver disease on ultrasound scans and/or FibroScans and those found to have iron overload on FerriScans will be referred to the liver clinics and haematologists respectively. All types of adverse events that occur from the day of randomisation to the end of follow-up will be reported to the sponsor and the participants’ usual clinical teams as soon as possible after the research staff identify the event. Participants will be given IV iron as per standard IV iron administration protocol post-trial as needed.

### Study outcomes {12}

#### The primary outcome

This will be involving an intention-to-treat analysis of the differences between the two study arms in the risk of hospitalisation with all-cause infection or death assessed in a time-to-first event analysis.

The primary outcome will be measured from the time of randomi**s**ation every **3** months to the end of the follow-up period.

